##### Training

All CGs will be trained in specific awareness and educational messages regarding heat prevention and adaptation measures to assist them in carrying out the sessions. Along with this, all CGs will be trained in the care of temperature devices, Android devices and data loggers and establishing a network within the community for effective surveillance of heat-related illness and hospital visits. The CGs will also be trained to effectively communicate with the community about structural intervention decisions and explain the reason for selecting a particular intervention for a structure.

##### Sessions

The community sessions will be led by CGs and held separately for males and females. It will consist of:

CG meetings (triggering session).Meetings supervised by research staff.

The sessions will focus on educating the community. The meeting schedule will be as follows:

Summer (April–June):Fortnightly community meetings.Weekly WhatsApp video messages.Weekly weather alerts.Late Summer (July–October)Monthly community meetings.Weekly WhatsApp video messages.Weekly weather alerts.Winter (November–March):Community meetings every other month.No WhatsApp video messages.

### Control arm

The control arm of the study will not receive any intervention other than routine care and information available through existing government response systems, including health and disaster management agencies.

## Data collection

Data collectors will undergo comprehensive training over a week to ensure a clear understanding of data collection tools, operational protocols, methodologies and management procedures. To assess their comprehension, they will complete practice questionnaires in the field and will also be trained in device and data management by experts.

### Line listing

The line listing and cluster assessment process is intended to establish a complete sampling frame for eligible clusters. A census of households will be done in the whole Bilal colony and Mehran town. The data collected will include household ID; number of floors in a structure (including basements, if any); total number of members, elderly, children and women of reproductive age (WRA) within a household; years lived within the same structure and primary material of floor and roof and wall. After the line listing, clusters of 90–120 households will be assigned a number by combining two to three streets depending on the number of households present in each street, which would result in approximately 300 clusters. We will then exclude clusters with inaccessibility or security concerns and for feasibility in terms of community cooperation and structural integrity for the proposed retrofitting interventions and the remaining clusters would then be randomised in the intervention and control groups.

### Cluster randomisation

We will employ a constrained randomisation procedure as described by Lock, Morgan and Rubin (2012),^36^ rather than relying on a single random allocation, the randomisation process will be implemented using the Stata ‘randomise’ command, which generates multiple allocation schemes in the background and evaluates balance across prespecified baseline covariates. An allocation achieving an acceptable level of balance between study arms at the cluster level will then be selected for the trial. Geographically designed clusters will be randomly assigned by an independent statistician to either the intervention arm, receiving the Heat Adaptation Bundle (ReHAB) or the control arm. Each random allocation is evaluated for covariate balance on three pre-specified characteristics: population residential density, household structural type (single-storey vs double-storey) and roof type (permanent, semi-permanent or natural materials).

Additionally, simple randomisation would be used to select eight households for the in-depth assessment from a subset in both intervention and control groups. Within these selected households, the Kish grid method would be used to randomly select the eligible adult if more than one adult is present. If the indexed participant refuses, the next eligible adult will be considered from the same household. If all eligible adults from a household refuse to participate, then another household will be included. Male and female participants for the subset will be selected systematically.

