### Study setting

Karachi has a tropical semi-arid climate where summers are sweltering, humid and evenings are breezy, while winters are brief, pleasant and arid, with clear skies most of the year and daily average temperatures ranging from 13°C to 34°C.^28^ In recent years, the temperature has regularly touched 40 °C and above for days and in June 2024, Karachi experienced the hottest day of the year, with temperatures reaching 47.2°C.^28^ This study will be conducted in representative urban settlements in Karachi (Bilal Colony and Mehran Town), which primarily comprises mixed construction typologies as most buildings are RCC structures or girder and concrete tiles with load-bearing block masonry walls, while some lower-income strata have semi-permanent constructions using concrete blocks, mud bricks or corrugated metal sheets.

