### Study design

This study is a 2-year prospective, cluster randomised controlled trial designed to evaluate the effectiveness of ReHAB intervention in urban, low-income settings. Clusters are defined as localities comprising 70–80 households which typically span one to two contiguous streets, and these clusters will be randomly assigned to either the intervention or control arm in a 1:1 ratio (figure 1). Due to the nature of the intervention, blinding of participants and researchers will not be feasible, but data analysis would be blinded. The trial is registered on clinicaltrial.gov with trial registration number NCT06991543. The study is planned to start from 1 January 2026 to 31 December 2027.

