### Statistical analysis

The trial has two co-primary outcomes, heat-related illness and quality of life. These outcomes will be evaluated independently to assess the effectiveness of the intervention. All statistical analyses will be conducted using STATA 18.0 (https://www.stata.com), following an intention-to-treat approach while accounting for the cluster-randomised trial design. Baseline characteristics will be analysed to assess comparability between intervention and control arms. Descriptive statistics will summarise household and participant characteristics, and any important imbalances at baseline will be adjusted for in the analysis. No interim analysis or formal stopping guidelines are planned given the low-risk nature of the intervention.

Statistical analyses will account for the cluster-randomised design by incorporating clustering through random effects or robust variance estimators, as appropriate. For outcomes measured repeatedly over time, within-participant correlation will be accommodated using repeated-measures mixed-effects models. Intervention assignment and seasonal variation will be included as fixed effects in all applicable models, while relevant baseline covariates and baseline outcome values (where available) will be adjusted for. Model assumptions, including overdispersion for count outcomes, will be assessed and alternative modelling approaches (eg, negative binomial models) will be used where appropriate. Missing data will be examined and handled using complete-case analyses or multiple imputations, depending on the extent and pattern of missingness. Sensitivity analyses will be performed to assess the robustness of findings to different assumptions regarding missing data.

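### Settlement is absent from the randomisation's balance criteria and is not named in any model, so a cheap gain in balance and precision is missed

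*Protocol article*

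**What the plan says.** The Study setting section places the trial in two named settlements, and the Line listing section builds the sampling frame from both: "A census of households will be done in the whole Bilal colony and Mehran town". Under Study design, "these clusters will be randomly assigned to either the intervention or control arm in a 1:1 ratio", which with 22 clusters means 11 per arm.

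The Cluster randomisation section describes constrained randomisation: many candidate allocations are generated and one with acceptable balance is chosen. The criteria are listed in full: "Each random allocation is evaluated for covariate balance on three pre-specified characteristics: population residential density, household structural type" (single or double storey), and roof type. No stratification by settlement is described.

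On the models, the Statistical analysis section says "Intervention assignment and seasonal variation will be included as fixed effects in all applicable models". The same sentence goes on to say that "relevant baseline covariates and baseline outcome values (where available) will be adjusted for". Earlier in that section, "any important imbalances at baseline will be adjusted for in the analysis". The Secondary outcome analysis section has a similar general provision for covariates. The primary model for heat-related illness is a Poisson regression with a random intercept for cluster. Settlement is neither listed nor ruled out as a covariate.

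**The concern.** With two sites and only 22 clusters, site is the obvious geographic variable to balance. It is known for every cluster before allocation. The three chosen criteria describe crowding and building form. They need not track influences shared across a settlement, such as water and power supply or access to health facilities. The Background itself ties strained water and energy supplies to heat stress, and hospital visits are an outcome.

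An allocation could therefore satisfy all three criteria and still put most of one settlement's clusters in one arm. If the settlements differ on an outcome, that draw moves the unadjusted arm contrast. Even with an even draw, a settlement difference that is not modelled stays in the between-cluster variance and costs precision. The list of criteria takes effect at allocation, so a later analysis plan can adjust for an uneven draw but cannot undo it.

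**Working it through.** **Inputs from the protocol (Sample size).** Control prevalence 28.9%; 30% relative reduction, so 20.23% and a target difference of 8.67 points; ICC 0.0122; 11 clusters per arm; 70 to 80 households per cluster; 10% attrition; two-sided 5% level; at least 80% power.

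**Assumptions, because the protocol gives no figures.** (a) The 22 clusters split 11:11 by settlement. (b) The three balance criteria are unrelated to settlement. (c) The settlement difference in prevalence is 2, 5, 7 or 10 points. (d) The prevalence scale of the sample-size calculation is used, although the primary analysis reports a rate ratio.

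**Step 1: the plan's own figure.** Individual randomisation needs 386 per arm. With 63 households (70 less 10%), the design effect is 1 + 62 × 0.0122 = 1.756. Then 386 × 1.756 ≈ 678 per arm, and 678/63 = 10.76, so 11 clusters. Power is 80.9% by normal approximation. The stated size is reproduced with no settlement term.

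**Step 2: chance of an uneven draw.** 11 of 22 clusters are drawn, and C(22,11) = 705,432.
- P(6:5) = 2 × 462² / 705,432 = 0.605, so P(7:4 or worse) = 0.395.
- P(exactly 7:4) = 2 × 330² / 705,432 = 0.309, so P(8:3 or worse) = 0.086.

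Unequal settlements are exposed too. If the smaller one has 5 clusters, a 4:1 or 5:0 division has probability 0.311. If it has 6, a 5:1 or 6:0 division has probability 0.149. To the extent that the three criteria track settlement, all these chances fall.

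**Step 3: shift in the unadjusted contrast.** Shift = (difference in cluster counts / 11) × settlement difference. For 7:4 the factor is 3/11.

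| Settlement difference | Shift at 7:4 | Share of 8.67 |
|---|---|---|
| 2 points | 0.5 | 6% |
| 5 points | 1.4 | 16% |
| 10 points | 2.7 | 31% |

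**Step 4: precision gained by adjustment, even draw.** An ICC of 0.0122 implies a between-cluster variance of 0.0122 × 0.289 × 0.711 = 0.00251, an SD of 5.0 points (about 25 points squared). A settlement difference d contributes (d/2)². If this is already inside the ICC and makes up a share s of that variance, the ratio of standard errors is √[(1 + 0.7564(1 − s)) / 1.7564], where 0.7564 = 62 × 0.0122.

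| d | (d/2)² | s | SE ratio | Cut in SE |
|---|---|---|---|---|
| 2 | 1 | 0.04 | 0.991 | under 1% |
| 5 | 6.25 | 0.25 | 0.945 | 5.5% |
| 7 | 12.25 | 0.49 | 0.889 | 11% |

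At d = 10 the contribution is 25, the whole between-cluster variance. That would leave no variation among clusters within a settlement, so it is an extreme case under the plan's ICC.

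**Step 5: why adjusting later does not fully replace balance.** With a 7:4 draw, arm and settlement are correlated at 3/11 = 0.273. Adjustment then inflates the variance of the arm effect by 1/(1 − 0.273²) = 1.08, about 4% on the standard error. With 8:3 the correlation is 5/11 = 0.455 and the factor is 1/(1 − 0.455²) = 1.26, about 12%. An even draw avoids this cost.

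**The case against.** The case on the other side is substantial, and much of it stands.

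- **The models are not closed.** A reader might infer that settlement is excluded from every model. The text does not support that. It commits to adjusting for relevant baseline covariates and for important imbalances, and an 8:3 division is the sort of imbalance it could cover. An exact covariate list commonly sits in the analysis plan, which is not shown. What remains is that adjustment prompted by an observed imbalance is decided after the fact, and it forgoes the precision gain when the draw happens to be even.
- **No bias.** A reader might infer that an uneven draw biases the trial. It does not: it is chance variation between clusters, which the random intercept is there to carry. The shift in Step 3 and the precision loss in Step 4 are largely two views of the same variance.
- **No shortfall in stated power.** The plan's ICC describes variation among the trial's clusters, so any settlement variance is plausibly already inside it, and Step 1 meets 80% without adjustment. A shortfall would need settlement variance on top of that ICC, which nothing in the document indicates. A rise in power from about 81% to 89% can be derived, but only from a difference near 7 points, picked so that settlement makes up half of the between-cluster variance.
- **No documented difference between the settlements.** The Study setting section gives them one shared description, and density, storeys and roof type may absorb part of any difference.

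None of this answers the omission from the list of balance criteria, which is stated in full and takes effect at allocation.

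**Conclusion.** The point holds as a cheap improvement that the design passes over. Settlement is missing from a closed list of balance criteria and is not named for adjustment. The stated sample size and power stand.

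The size rests on assumption. With an 11:11 split and criteria unrelated to settlement, there is about a 39% chance of a 7:4 or worse division and about a 9% chance of 8:3 or worse. The resulting shift at 7:4 and the precision gained by adjustment both run from negligible, if the settlements differ by 2 points, to worthwhile at 5 points or more. The protocol does not show where in that range the trial lies. The change is worth making because it costs almost nothing and its allocation half is lost once clusters are assigned.

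**What to change.** - **Cluster randomisation:** stratify the constrained randomisation by settlement, splitting clusters as evenly as possible between arms within Bilal Colony and within Mehran Town, and apply the three existing criteria inside that restriction. Alternatively, add settlement as a fourth balance criterion.
- **Statistical analysis:** pre-specify settlement as a fixed effect in the arm comparisons, so that it does not depend on an observed imbalance.
- **If allocation has already been done:** make only the model change.

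Cost: one restriction in the randomisation code, one covariate, and about one of 20 cluster-level degrees of freedom. No new data are needed, because the census already places every cluster in a settlement.

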### Household data collection

Baseline, monthly/weekly follow-up and end line surveys will be conducted in 22 randomised intervention and control clusters. Baseline and endline surveys will be done to collect information on various variables, including demographics (household size, socioeconomic status, education, occupation, ethnicity), healthcare seeking, mental health using the WHO wellness survey, food security, dietary diversity, co-morbidities, medications, signs and symptoms of heat-related illness (box 1). The questionnaire was developed using standardised questionnaires used during similar surveys, and some questions were modified to better accommodate local contexts. The tool was then translated into the local language and back-translated to English to validate the translation.

Box 1Section for data collection toolDescription of modules and their sectionsModule-A: Household Identification and Demographic InformationSection-A1: Household Identification and ConsentSection-A2: Household Members’ InformationSection-A3: Socioeconomic Status of Household (SES)Section-A4: Building SurveySection-A5: Household Water and Sanitation StatusModule-B: Household Food Insecurity, Dietary Diversity and Source AssessmentSection-B1: Household Food Insecurity Experience ScaleSection-B2: Household Dietary Diversity and Source AssessmentModule-C: Health and Hygiene Assessment of Adult ParticipantsSection-C1: General Health and DisabilitiesSection-C2: Mental HealthSection-C3: Hygiene Practices (Hand Washing, Dental Hygiene, Bath, (Menstrual Hygiene for Female)Module-D: Heat Exposure/Sleep/Dietary AssessmentSection D1: Work and Sun ExposureSection D2: At-home heat exposureSection D3: Heat Stress Experiences, Food Security and Adaptation StrategiesSection D4: Knowledge About Heat-Related Health Problems, Existing Heat Adaptation and Prevention StrategiesSection-D5: SleepSection-D6: Quality of life

Data on the signs and symptoms of heat-related illness will be collected through multiple points to ensure no event is missed during the study period. Data collectors will conduct weekly household visits to collect symptom data. Events identified through community surveillance will trigger a household visit by data collectors who will use the same survey tool, and reported health facility visits will be verified through facility records where feasible. Symptoms will be classified as International Classification of Disease-11 and institutional classification of heat illness (figure 2). Data for quality of life will be acquired through multiple surveys of all households included and the respondent for these surveys will be the selected index adult (table 3).

Additionally, at endline, 5 mL of venous blood samples will be collected by trained phlebotomists using standard aseptic techniques from control and intervention households during peak heat in year two of the project. These samples will be stored for further evaluation in our biobank following standard storage guidelines. They may be used to detect heat-related biomarkers in any future research.

Quantitative data collection will be conducted using handheld devices equipped with a customised application developed in Java, using MySQL and SQLite for data storage. The programme will incorporate range and consistency checks, along with skip patterns to reduce data entry errors. Any detected inconsistencies will be addressed by contacting data collectors for verification and correction. Each participant will be assigned a unique code generated by the Android application to ensure anonymity. All data will be securely stored behind firewalls and fully anonymised before analysis.

### Environmental data collection

Environmental data collection will include a thermal drone survey to assess the comparative heat accumulation and dissemination of each structure. A drone survey of each cluster will be conducted before intervention and once yearly at three points, that is, at sunrise (within 2 hours), mid-day (between 12:00 and 16:00) and sunset (1 hour before sunset and 1 hour after sunset).

Indoor temperatures of all households included will be recorded using thermochron iButtons set to record temperature at 20-min intervals. Outdoor temperatures and humidity will be recorded using HOBO weather stations installed at each site and Kestrel drop devices (also recording at a 20-min interval). Additionally, local weather station data will be used to obtain daily information on ambient temperature, relative humidity, wind speed and solar radiation throughout the study period. Heat stress will be calculated by integrating these parameters to formulate heat indices, including the Universal Thermal Climate Index (UTCI) and the Wet Bulb Globe Temperature.

Designated personnel will regularly retrieve environmental data from wearable and installed devices, returning them to participants after each data transfer. In areas with limited internet access, the team leader will manually export the data onto a USB device and store it securely on a password-protected laptop to prevent data loss. All data will be archived in a secure repository at Aga Khan University (AKU), Karachi, with access restricted to authorised data management personnel through AKU-LAN identification. Role-based access permissions will be implemented to ensure confidentiality and data security. To prevent data loss or corruption, the repository will be synchronised daily with a secure remote backup system.

### Devices

The devices and their utilisation for outcome measurements are provided in table 2:

**Table 2 T2:** Devices used for outcome measures

Device	Outcome measures	Placement
Thermochron ibuttons, Temp-U, which record temperature and humidity	Individual and household-level exposure	Put it at select households in the intervention and control clusters within the main living room, midway between floor and ceiling and away from any direct heat source. Devices will be given to individuals selected for the sub-group for individual exposure assessment
Kestrel 5400, which will record multiple environmental parameters like wet bulb globe temperature (WBGT), solar radiation, barometric pressure, wind speed and humidity	Environmental exposure	One device rotated in each cluster
Fitbit Inspire 3 is a wearable fitness tracker that will track heart rate, sleep cycles, activity levels and energy consumption	Individual physiological outcomes	Given to the sub-set population selected in the intervention and control clusters
Kestrel drop D2 and HOBO U-30 weather stations	Weather	One weather station placed at the field office as a central location and one Kestrel drop D2 placed in each cluster

### Data collection from subset population

Monthly data will be collected for in-depth understanding of heat stress and intervention effectiveness within the subset population (table 3). This will include thermal comfort, mental health and heat exposure assessment.

**Table 3 T3:** Schedule of outcome assessments and follow-up activities

Parameter	Time points	Details	Devices/Tools	Population/Unit
Primary outcomes				
All heat-related illness	Weekly during peak summers	Heat-related illnesses	Weekly community survey, health facility data, community surveillance	All members of included households
Quality of life	Mid of April, July and December for two consecutive years	Quality of life mean score	WHOQOL-BREF* questionnaire	Indexed adults of all included households
Secondary outcomes				
All-cause mortality	Weekly during peak summers	Any mortality occurring within the included clusters	Weekly community survey, health facility data, community surveillance	All members of included households
Hospital visit/hospitalisation	Weekly during peak summers	Any hospital admission or hospital visit occurring within the included clusters	Weekly community survey, health facility data, community surveillance	All members of included households
Indoor heat index	Continuous throughout the year	Indoor data loggers	iButton, Kestrel Drop D2, Temp-U	All included households
Thermal comfort (home)	Monthly	Self-reported comfort levels	Thermal comfort survey adapted from CHEQ-5†	Indexed adults randomised for sub-group
UTCI§	Continuous throughout summers	Outdoor only	Kestrel Drop D2, Kestrel 5400, HOBO weather station	Overall catchment area
Outcomes measured for subset of population				
Personalised heat exposure	Baseline, monthly	Occupation, sun exposure, illness history, daily routine	Structured survey tool (adapted from HotHaps)‡ and Temp-U	Indexed adults randomised for sub-group
Physiological strain markers	Continuous throughout summers	Heart rate, sleep cycles, VO₂¶ max	Fitbit Inspire 3	Indexed adults randomised for sub-group

* WHOQOL-BREF: World Health Organization Quality of Life - Brief

† Cold and Heat Exposure Questionnaire

‡ High Occupational Temperature Health and Productivity Suppression

§ Universal Thermal Climate Index

¶ Volume of Oxygen

Individual heat exposure of a subset of participants (eight per cluster) will be measured by attaching a thermochron ibutton or Temp-U to their clothing. The participants will be instructed to always wear this logger. At the time of sleeping, they will be instructed to place the logger on their bedside.

The participants from the sub-set will be provided with Fitbit Inspire 3 devices to record physiological markers: heart rate, daily body temperature change, sleep, energy expenditure and activity. These smartwatches will be synced to the AKU server weekly and returned to the participants after charging.

Participant compliance will be monitored through spot checks and periodic review of device data. For Fitbit devices, heart rate data will be reviewed, as prolonged absence of heart rate recordings may indicate that the device was not worn. Similarly, iButton and Temp-U data will be checked periodically for implausible temperature spikes or sudden drops, which may indicate non-compliance or incorrect device use.

